### Procedure

Site investigators from the research team will work with the support of members of the team of substance misuse practitioners working in the prison to inform potential participants of the study. Site investigators will be responsible for completing screening, consent and randomization. Site investigators and practitioners will be responsible for conducting baseline and 4-week post-baseline assessments. Practitioners will be responsible for delivering both BFO and the standard treatments received by the two study groups. Site investigators will be responsible for conducting 3- and 6-month follow-up assessments. All site investigators and practitioners have been vetted and security cleared to work in prisons by HMPPS and have enhanced clearance via the UK Government Disclosure Barring Service. The site investigators have trained all participating practitioners in delivering BFO as CAT and have also conducted training around RCT methodology. All practitioners are trained and experienced facilitators of structured substance misuse interventions. Both site investigators and practitioners have received training in ethics and confidentiality issues when working with offenders in secure settings.

All prospective participants that potentially meet the study criteria will be informed of the study’s objectives and requirements using the Participant Information Sheet and Informed Consent Form before any screening procedures are performed. If willing to participate in the study, participants will be requested to provide written consent after being given sufficient time to consider their participation and having had the opportunity to ask for further details. During the informed consent procedure, participants will be provided with information about the fact they can withdrawal from the study at any time without giving a reason, and without their withdrawal affecting their recovery and rehabilitation support. Additionally, they will be assured that when their data are collected, no identifiable information can be traced back to them, and that their data will be fully anonymized.

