The Informed Consent Form will be signed and dated by both the participant and the site investigator, and the participant’s preferred mode of contact (e.g. telephone, email etc.) and contact details for the completion of follow-up assessments will also be noted at this point. The participant will be provided with a copy of the signed consent form and the Participant Information Sheet. The original consent forms will be retained in a secure storage facility separately from source data to protect against breach of privacy and participant anonymity.

If written consent is given, each participant will then be screened for eligibility by the site investigator before then being randomized to either the BFO or control group. Randomization will occur at the level of the individual participants, with participants being assigned to one of the study groups following the generation of a random allocation sequence via the *Research Randomizer* (from the Social Psychology Network- Urbaniak and Plous 2011). Sequentially-numbered opaque sealed envelopes containing the treatment group that the participant will be allocated to will be delivered to the research site prior to commencement of the study. The participant number will be determined according to the order of enrolment in the study. The site investigator will assign and open one sealed envelope per participant. A screening log, including the participant number and treatment group assigned by randomization and any subsequent reason/s for exclusion from the study (if applicable), will then be completed by the site investigator.

No longer than 2-weeks after being randomized and completing the eligibility screening, both study groups will complete a battery of assessments to collect data around primary and secondary outcomes and demographic information including age and ethnicity. This battery of assessment will be delivered digitally via desktop computers within the prison IT suites. The assessment for the BFO group will be completed within the BFO program. The control group will complete the measures via a specially developed digital assessment platform which will deliver the same assessment that is included in the BFO program, but without providing access to any of the digital intervention content provided by BFO.

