Study groups will then complete a period of 4-weeks of substance misuse treatment, of either i) BFO plus standard treatment, or ii) standard treatment only. For the BFO group, the 4-week intervention will be delivered to groups of approximately 10 participants at a time, so it is estimated that approximately 6–8 groups will need to run successively to achieve the sample size required, in order to account for some attrition between baseline and 4-week post-treatment assessments. BFO group participants will receive two sessions of BFO each week, alongside any standard treatment they may be engaging with.

Online access to the BFO program is granted via the activation of an access code given to the participant at the alcohol and drug misuse service by authorized practitioners. To activate the access card and create a personal account, the participant must enter a username and password of his choice along with the access code. The practitioners will be able to assist with the online access if required. The participants must also agree to the Terms & Conditions of using BFO, which are in accordance with the Participant Information Sheet and Informed Consent Form and conform to the European Union General Data Protection Regulation around the use of digitally captured personal data. The practitioners must ensure that they log out of BFO at the end of each treatment session to protect the confidentiality of the data.

Procedures to enhance retention of participants during the 4-week treatment period will include practitioners providing ongoing support during weekly key-working sessions, which all offenders in the prison will routinely receive during the standard substance misuse treatment. When participants do dropout of the study, new participants will be recruited and randomized to replace dropouts, in order to ensure the required sample size of 120 participants (60 per group) complete the 4-week treatment period and provide post-treatment data. However, in line with ITT principles, all randomized participants, including dropouts, will be included in the final analyses (see ‘Data Analysis’ section). After completion of the 4-week treatment period, participants in both groups will complete the same battery of digital psychometric assessments on the prison desktop computers.

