Follow-up assessments will then also be completed at 3- and 6-months post-treatment with all participants. Follow-up assessments may be completed either in the community if offenders have been released, or in prison if they are still serving their sentence. The site investigators will work with the practitioners delivering both BFO and standard treatments to determine which participants have been released back to the community since completing their 4-week treatment period, and which participants are still serving their sentence in the participating prison. Additionally, those participants who have been transferred to a different prison will also be identified.

Depending on participants’ preference, the site investigators will contact all participants who have been released back to the community via telephone or email, and their assessment will be completed either over the phone, or via a link to an online version of the assessment. The preferred contact details for each participant that were collected at the time of consent and randomization will be used. For those participants who are still serving a prison sentence, or have been reconvicted and are serving a new sentence, or have been transferred to a different prison, they will be visited by the site investigator at their current prison and their follow-up assessment will be completed there.

By following the procedure described above, each participant will take part in the study for a total of approximately 7-months, including 4-weeks of treatment and 3- and 6-month follow-up assessments. It is likely that the study will run for a total of approximately 18-months, which will include enough time for recruitment, running enough successive 4-week long BFO groups to achieve the required sample size, and completion of all 3- and 6-month follow-up assessments.

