### Data analysis

Quantitative data will be analyzed and reported using SPSS® Version 25.0 (or later) with all analyses to be performed as per the statistical analysis plan. The appropriate 95% - confidence interval will be applied. The *all-randomized population* will consist of all participants in the study that have been screened and allocated to either the i) BFO plus standard treatment, or, ii) standard treatment only group. The *per-protocol population* will consist of all participants randomized into the study who have completed the 4-week treatment period as well as all follow-up assessments.

Analyses will be performed on the basis of an ITT population, with the all-randomized population included in the analyses. No participants will be excluded from the ITT analyses, i.e. those who have withdrawn, been lost to follow-up, or have provided incomplete outcomes data. Separate analyses will also be conducted on the per-protocol population who have provided at least one set of follow-up data. Outcomes from these two analyses (ITT, per-protocol population) will be compared to examine whether missing data may have had an impact on reliability of conclusions formed around comparative effectiveness of the two study conditions.

Previous analyses (e.g. Elison et al. 2015a, b, c) indicate that data will likely be non-normally distributed in which case nonparametric repeated-measures analyses of covariance (ANCOVA) using appropriate distribution such as Poisson distribution, will be used to compare the study groups at 4-weeks post-treatment and 3- and 6-months follow-up on self-reported substance use, substance dependence, mental health sequelae, biopsychosocial functioning and quality of life. However, normality will be tested when data are available for analyses, and appropriate distributions will be applied.

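### The 4-week assessment is tied to completing treatment and, on a fair reading, to the BFO software in one arm only, so men who disengage from BFO risk being missed more often than controls who stop treatment

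*Protocol article*

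**What the plan says.** All of this is in the Protocol article.

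- **Trigger and place (Procedure).** The visit is introduced with "After completion of the 4-week treatment period, participants in both groups will complete", and the full instruction is that "participants in both groups will complete the same battery of digital psychometric assessments on the prison desktop computers". No other place or route is given for this visit.
- **Another description of the same visit (Procedure).** Earlier in the section, investigators and practitioners are "responsible for conducting baseline and 4-week post-baseline assessments", which counts time from baseline.
- **Platform (Procedure, on the baseline battery).** "The assessment for the BFO group will be completed within the BFO program". By contrast, "The control group will complete the measures via a specially developed digital assessment platform", which carries the same assessment without intervention content.
- **Replacement (Procedure).** If men drop out, "new participants will be recruited and randomized to replace dropouts", until there are 60 per group who have both finished the four weeks and given data afterwards.
- **Later visits (Procedure).** Telephone, an online link, or a visit to the man's current prison are offered at 3 and 6 months, for all participants.
- **Analysis set (Data analysis).** "No participants will be excluded from the ITT analyses".

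**The concern.** An intention-to-treat comparison needs outcomes from men who stopped treatment as well as from those who finished. The week-4 arrangements make those outcomes harder to get, and not equally so in the two arms. If the BFO battery stays inside the program at week 4, a man who has stopped engaging with BFO has to log back in to the treatment he left in order to be measured. A control who stops standard treatment faces no such step, because his platform is separate from his treatment. The replacement rule adds to this: it steers recruitment by a single count of men who complete treatment and supply data, so nothing in it prompts staff to pursue a man who has stopped.

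The battery contains the primary outcome, self-reported substance use. Week 4 is one of the three comparison points in Data analysis, and the target of 60 per group is defined there. If the men missed in one arm are those doing worse, the observed week-4 comparison favours that arm. A model using baseline and later data can reduce this only under assumptions about the missing values. Comparing the intention-to-treat and per-protocol results is a weak check, because neither set observes week-4 outcomes in men who were never assessed.

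**Working it through.** **1. The plan's own figure.** Power calculation asks for 120 evaluable men with 50% attrition: 120 / (1 − 0.5) = 240, as stated. That allowance is assigned to 3 and 6 months. The present point does not depend on it.

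**2. BFO loss by week 4 that the plan implies.** Procedure expects 6 to 8 successive BFO groups of about 10 men, to allow for attrition before the 4-week assessment, with 60 completers needed. Loss = 1 − 60 / (10 × groups):

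- 6 groups: 1 − 60/60 = 0%
- 7 groups: 1 − 60/70 = 14%
- 8 groups: 1 − 60/80 = 25%

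Both inputs are approximate in the text. No corresponding figure is given for controls.

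**3. Can release explain much of the loss?** Participants requires at least 3 months (about 13 weeks) left at the study prison. Baseline follows randomization by at most 2 weeks and treatment lasts 4, so the visit falls at about 2 + 4 = 6 weeks. Planned release should rarely come first. Transfer or removal still could, but nothing in the text makes that differ by arm.

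**4. Size of a possible bias (illustration only).** Let L be the fraction of an arm missing at week 4 and g the amount, in SD, by which missing men are worse than observed men. The full-arm mean is worse than the observed mean by L × g. Comparing observed means therefore gives

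bias in favour of BFO = (L for BFO − L for control) × g.

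The control loss and g are assumptions; the protocol gives neither. With BFO loss at the top of its range, 25%:

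| Control loss | g = 0.25 SD | g = 0.5 SD | g = 0.8 SD |
|---|---|---|---|
| 0% | 0.0625 | 0.125 | 0.20 |
| 10% | 0.0375 | 0.075 | 0.12 |
| 25% | 0 | 0 | 0 |

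If controls were lost more often, the sign would reverse: BFO 10%, control 25% and g = 0.5 give (0.10 − 0.25) × 0.5 = −0.075 SD.

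**5. What that does to the test.** With 60 observed men per arm, the standard error of a standardized difference is √(2/60) = 0.183. A bias of 0.075 SD is 0.075 / 0.183 = 0.41 standard errors, and the two-sided 5% test then rejects a true null about 7% of the time. A bias of 0.20 SD is 1.10 standard errors, giving about 20%. These are unadjusted comparisons of observed men. The planned baseline-adjusted repeated-measures analysis could do better to the extent that baseline and later data predict the missing values.

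**The case against.** The strongest reply is that the protocol does not bar anyone from assessment. It speaks of dropping out of the study, not of BFO, and no sentence says that a man who stops BFO goes unmeasured. The completion wording can mean the end of the four-week window. The description counted from baseline supports that, and so does Standard treatment, where courses run about 4 to 12 weeks, so many controls will not have finished treatment at week 4. This stands as far as it goes: it shows that the calendar reading is available. It also leaves one visit described in two ways, while the replacement rule leans towards the completer reading.

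On the platform, the arm-specific statement is made for baseline and not repeated for week 4. Logging in for a questionnaire is not attending a session, practitioners can help with access, and controls must come to the same desktops. That makes the asymmetry modest. It does not remove it, since the same battery is specified at week 4 and no other platform is named for the BFO arm.

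Three stronger readings are tempting and not supported:

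- **That men who stop BFO will lose their outcome, and that loss will differ by arm.** The text gives no loss by arm; this is a risk inferred from the arrangements.
- **That leaving prison early drives the problem.** The 3-month criterion makes planned release before week 4 rare, and any departure would affect both arms alike.
- **That later follow-up traces completers only**, because investigators establish "which participants have been released back to the community since completing their 4-week treatment period". That phrase marks a time. The same part of the Procedure plans the 3- and 6-month visits for all participants, with off-site routes.

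It may also be said that an article leaves visit logistics to the full protocol. That would answer silence, but the trigger, place, platforms and replacement target are all stated here.

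**Conclusion.** The point holds as a risk confined to week 4. The stated trigger, the place, the software holding the BFO battery and the combined completion-and-data target together make it easier to miss men who disengage from BFO than controls who stop treatment. Analysing all randomized men cannot replace values that were not collected.

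The size is unknown. The plan's group count allows BFO loss anywhere from 0 to 25%, and nothing is said about control loss. Over the range shown for 25% BFO loss and control loss no higher than that, the bias runs from zero to about 0.20 SD in favour of BFO. The upper end needs 25% loss against none and dropouts 0.8 SD worse. The direction depends on which arm loses more men and on early stoppers doing worse in a way that baseline does not explain. The conclusion also rests on reading the baseline platform statement as carrying over to week 4.

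**What to change.** In Procedure:

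1. State that the 4-week assessment is due at a fixed time from baseline for every randomized man who has not withdrawn consent to assessment, whatever his attendance. This agrees with the section's own description of the visit as counted from baseline.
2. Give the week-4 outcome battery in both arms on the stand-alone platform already built for controls.
3. Allow the telephone, link and prison-visit routes, now described for 3 and 6 months, at week 4 for men who have been transferred or released.
4. Record stopping treatment separately from withdrawal from the study.

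The cost is a few sentences, wider use of an existing platform, and a small number of extra week-4 contacts by routes and contact details the trial already plans to have. The baseline assessment inside BFO can stay, since the program uses it for tailoring. BFO men would then change platform between baseline and week 4, but the protocol says the two platforms deliver the same assessment.

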### Measures

The primary outcome will be self-reported substance use which will be calculated using answers to two questions i) ‘on a typical day, how many (unit of measurement) of (substance) are you using?’, and ii) ‘in a typical week, how many days are you using (substance)?’. Given the research setting, i.e. a Category D ‘open prison’ where offenders spend time in the community each week, it is more likely that any substance use outcomes will be due to genuine treatment effects, than they would be in a more highly secure prison setting with fewer opportunities to access and use substances. Information about weekly substance use before each participants’ current prison sentence will also be collected.

A number of secondary outcomes will also be measured and will come from standardized psychometric assessments of biopsychosocial functioning, which will include:i)Severity of substance dependence: This will be measured using the Severity of Dependence Scale (SDS; Gossop et al. 1995), which is a 5-item, 4-point Likert scale measuring psychological dependence on illicit drugs, that has been previously used in studies of persistent drug use in prison populations (Strang et al. 2006) and studies of programs to address substance related offending behaviors (Crane and Blud 2012). It has been demonstrated to have excellent reliability with an alpha coefficient of .89.ii)Mental health sequelae: This will be measured using the Patient Health Questionnaire (PHQ-4; Kroenke et al. 2009), which is a 4-item, 4-point Likert scale measuring depression and anxiety, which has been demonstrated to have excellent internal reliability (alpha = .81), with scores on the PHQ-4 having been demonstrated to converge with scores on other measures of anxiety and the 20-Item Short Form Health Survey.iii)Quality of life: This will be measured using 5 items from the World Health Organization Quality of life measure (WHOQoL-BREF; Skevington et al. 2004): A total of 5 items (items 1, 2, 17, 18, 20) from the WHOQoL-BREF have been selected for measuring general quality of life. Taken as a whole measure, the WHOQoL-BREF is a 26-item, 5-point Likert scale containing items measuring 4 main domains - physical, psychological, social and environmental life satisfaction. As only the first 5 items of the WHOQoL-BREF are being used, reliability and validity analyses will be conducted on data generated from these 5 items. Internal reliability which will be examined using Cronbach’s alpha, and concurrent validity will be examined by correlating scores on the 5 WHOQoL-BREF items against scores on the other measures included in the study measuring constructs related to quality of life.iv)Biopsychosocial functioning: This will be measured using the Recovery Progression Measure (RPM; Elison et al. 2016a, b; Elison et al. 2017a, b, c, d), which is a 36-item measure comprising 6 ‘impact slider’, 11-point Likert scale items each measuring level of severity of impairment in the following 6 domains of functioning; difficult situations, negative thoughts, emotions, unhelpful behaviors, physical sensations, lifestyle. In addition, the RPM contains 30 dichotomous ‘yes/no’ response items measuring presence or absence of specific biopsychosocial issues within each of the 6 domains. Statistical standardization analyses based on a sample of 2218 service users seeking support for substance misuse found the overall RPM scale to have excellent reliability with an alpha coefficient of .89. The RPM has also been found to be a valid measure with scores from 9208 service users converging significantly with those on standardized psychometric measures of mental health and substance dependence (*p* < .0001).

In addition to the standardized measures described above, socio-demographic data will also be collected via the digital assessment completed by both study groups, including age and ethnicity. Additional socio-demographic data will be collected via paper/pen assessment when participants are first randomized, including educational level achieved, employment status before entering prison, and marital status (See Additional file 1: Appendix A), and what standard treatments each participant has received (see Additional file 1: Appendix B). This will allow comparisons of the two study groups to be made, and also comparisons of all participants with data published each year by the UK Ministry of Justice describing the broader prison population in England and Wales.

When follow-up assessments are conducted at 3- and 6-months, each participant will also be asked about any further involvement with criminal justice authorities since being released from prison, if they have been released from prison in the interim, and if so, the nature of this involvement with the authorities, e.g. being arrested, any court appearances etc. (See Additional file 1: Appendix C). For ethical and legal reasons, these questions will be restricted to questions that enquire as to criminal justice system involvement only, as opposed to asking participants about any crimes they may have committed that may not have been discovered by the authorities.

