### Participants

Participants included in the study will be offenders currently serving a prison sentence aged 18 to 65 years with problem alcohol and/or drug use of duration of 12-months or longer. This period of time is in line with DSM-V criteria for substance related disorders (American Psychiatric Association 2000). It is estimated that a total of 240 participants will need to be recruited and screened in order to obtain a sample of 120 evaluable participants (see ‘Power Calculation’).Inclusion criteriaMale offenders currently serving a prison sentence with problem alcohol and/or drug use aged 18 to 65 years.Willing and able to give informed consent for participation in the study.Has at least 3-months left to serve of their sentence at the prison acting as the research site, at the time they are recruited to the study.Problem alcohol and/or drug use present for at least 12-months prior to current prison sentence.Willing to follow treatment for problem alcohol and/or drug use for 4-weeks.Willing to provide outcome measures at 3- and 6-months follow-up.Concomitant alcohol and drug/s use permitted, as well as any prescribed medication.Exclusion CriteriaParticipation in any other alcohol and/or drug related clinical studies.Individuals detained under the Mental Health Act.Individuals with a known and diagnosed intellectual or developmental disability.Non-English speaking offenders (study information material and program only produced in English).

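### The primary-outcome questions name no recall period, so the 3- and 6-month scores mix opportunity to use with treatment effect across open prison, community and closed custody

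*Protocol article*

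**What the plan says.** The Measures section of the Protocol article derives self-reported substance use, the primary outcome, from two questions: "on a typical day, how many (unit of measurement) of (substance) are you using" and "in a typical week, how many days are you using (substance". Both are in the present tense and neither states a period. The one dated use item is "Information about weekly substance use before each" man's current sentence, which covers no time after randomization.

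On timing, the Procedure section says "Follow-up assessments will then also be completed at 3- and 6-months post-treatment with all participants". On place, it says "Follow-up assessments may be completed either in the community if offenders have been released, or in prison if they are still serving their sentence". Released men answer by telephone or online link. Men who are still serving, "or have been reconvicted and are serving a new sentence, or have been transferred to a different prison", are seen at whichever prison holds them.

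The Setting and Measures sections justify an open prison by opportunity: because these men spend time in the community, "it is more likely that any substance use outcomes will be due to genuine treatment effects" than would be so in a more secure prison. Temporary-release (ROTL) status is the only opportunity variable to be taken into account, and it is recorded once, at the first treatment session. The Data analysis section compares the groups at 4 weeks, 3 months and 6 months and adjusts for baseline scores. The entry criterion on remaining sentence is "Has at least 3-months left to serve of their sentence at the prison acting as the research site", judged at recruitment.

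**The concern.** The argument from opportunity supports the outcome only while every man is in the open prison. That is so at baseline and at 4 weeks, which are both completed on the prison's own computers. It no longer holds at 3 and 6 months, when the same undated questions reach men in settings that, on the protocol's own reasoning, differ in access to substances.

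Two men with the same course after release could then score differently. One relapses and is still at liberty, and reports his present heavy use. The other relapses, is reconvicted, and is asked in closed custody what he uses in a typical week; he may truthfully give a low figure. Adjusting for baseline scores cannot correct for a setting that arises after randomization, and no later analysis can recover use that was never asked about.

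At stake is whether the 3- and 6-month comparisons of the primary outcome measure a change in use or partly a change in access.

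**Working it through.** No figure in the plan bears on this point, so there is none to reproduce. The check has two parts.

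**1. Are mixed settings likely at follow-up, or only possible?**

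Inputs: baseline up to 2 weeks after randomization and treatment of 4 weeks (Procedure); follow-up 3 and 6 months after treatment (Procedure), taken as 13 and 26 weeks; at least 3 months, about 13 weeks, left to serve at recruitment (Participants). I assume that recruitment and randomization coincide and that treatment starts straight after baseline.

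- 3-month visit: from 0 + 4 + 13 = 17 to 2 + 4 + 13 = 19 weeks after randomization.
- 6-month visit: from 0 + 4 + 26 = 30 to 2 + 4 + 26 = 32 weeks.
- A man at the entry minimum may leave at about 13 weeks, which is 4 to 6 weeks before the first follow-up and 17 to 19 weeks before the second.

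The entry rule therefore admits men who will be out before both visits. The Procedure section also plans explicitly for released, transferred and reconvicted men.

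**2. What could this do to the comparison?**

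All rates here are assumed, because the documents give none. Let *r* be the relapse risk in an arm, *q* the share of relapsed men in closed custody at the visit, 5 the days per week used by a relapsed man at liberty, and *c* the days per week reported by a relapsed man in custody. Men who have not relapsed report 0.

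Mean days per week in an arm = *r* × [(1 − *q*) × 5 + *q* × *c*]

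Take *r* = 0.50 (control) and 0.35 (BFO). With nobody in custody the means are 0.50 × 5 = 2.50 and 0.35 × 5 = 1.75, a true difference of 0.75.

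| *q* control / BFO | Difference, *c* = 0 | Share of truth | Difference, *c* = 1 | Share of truth |
|---|---|---|---|---|
| 10% / 10% | 2.250 − 1.575 = 0.675 | 90% | 2.300 − 1.610 = 0.690 | 92% |
| 20% / 20% | 2.000 − 1.400 = 0.600 | 80% | 2.100 − 1.470 = 0.630 | 84% |
| 30% / 30% | 1.750 − 1.225 = 0.525 | 70% | 1.900 − 1.330 = 0.570 | 76% |
| 30% / 10% | 1.750 − 1.575 = 0.175 | 23% | 1.900 − 1.610 = 0.290 | 39% |
| 40% / 10% | 1.500 − 1.575 = −0.075 | −10% | 1.700 − 1.610 = 0.090 | 12% |

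When *q* is the same in both arms and *c* = 0, the formula reduces to 5 × (1 − *q*) × (difference in *r*). The loss is then exactly the share *q*, whatever the relapse risks. Larger losses need custody among relapsed men to differ by arm.

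The calculation covers frequency only. The actual outcome also uses amount per day, and the documents give no values for that either.

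**The case against.** Several points on the other side have force.

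- **The item says typical, not current.** A recently returned man may describe his usual pattern at liberty. A reader might infer that he is bound to score low, but the wording does not support that. What is shown is ambiguity: similar men may answer about different periods.
- **Custody does not mean no use.** The Setting section and the Discussion both say that use persists even in the most secure prisons. The *c* = 0 column is an extreme, and transfer to another prison is not stated to mean a closed one.
- **The pathway may be uncommon.** It needs release, relapse, reconviction and return before a visit. About 75% of the men serve 4 years or longer, the Discussion calls open-prison men generally low-risk, and 3 months left is a minimum. This limits the likely size. It does not settle it, because total sentence length does not say how much is left, and this is a resettlement prison.
- **Part of the information is collected.** Investigators will establish where each man is, criminal justice involvement is asked about at follow-up, and post-release offending is a secondary outcome. But nothing in the article links these to the use score.
- **The analysis plan is not shown.** A sensitivity analysis may be in it, so its absence here is no fault. The wording of the questions is different: the article gives it verbatim, and an analysis plan cannot supply a recall period to answers already given.

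A reader might also infer that the treatment effect could well be reversed. That is not supported. In the table the sign changes only at 40% against 10% in custody with no use at all inside; at one day per week inside, it does not change. Nothing in the documents supports that gap between the arms.

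**Conclusion.** The point stands as a should-fix. The primary-outcome questions have no recall period, the 3- and 6-month assessments are spread over settings that the protocol itself regards as differing in opportunity, and the article describes no safeguard beyond ROTL status recorded once at the start. The follow-up scores therefore mix opportunity with treatment effect.

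The expected consequence is dilution of the 3- and 6-month comparisons: in the illustration, 10% to 30% of the true difference when custody among relapsed men is equal across arms and they report no use. Dilution is greater if return to custody differs by arm, which is conceivable because the Background describes the program as aimed at offending as well as substance use. All of this rests on assumed rates, and the true size is unknown.

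A reader might take the whole primary comparison to be compromised. It is not: the 4-week assessment takes place in the open prison and is largely unaffected.

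**What to change.** 1. Put the same fixed look-back into both questions at all four assessments, for example days used and amount per using day in the last 28 days.
2. At each follow-up, record the setting (open prison, community, closed prison) and the number of days in that window spent in closed custody. The look-back alone is not enough, since a man held for the whole window may still report low use; these fields make such scores identifiable.
3. Add a sensitivity analysis of the 3- and 6-month comparisons in which men returned to custody are not counted as improved.
4. If wanted, ask men in closed custody about their last period at liberty as a supplementary item. Do not substitute the answer into the primary score: they would then report an earlier period than everyone else, and the quantity estimated would change from recent use to use when last at liberty.

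The cost is rewording two questions, a few extra form fields and one additional analysis, with slightly less comparability with earlier studies of the program. The rewording has to be in place before the assessments it is meant to protect.
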